#### Criteria

Adult (≥18 years) patients with acute thermal burns who are admitted for at least 24 hours or scheduled for surgery are eligible for this study, when the criteria listed below are met.

Inclusion criteria:

Burns with a size of >2.5 centimetres diameter;LDI scan indicating:
Deep partial-thickness burn: yellow wound area on LDI with healing potential between 14 and 21 days, or;Mixed superficial and deep partial-thickness burn: mixed red and yellow wound area on LDI, with a demarcated predominantly yellow area of at least 25cm^2^, or;Mixed full-thickness and deep partial-thickness burn: mixed blue and yellow wound area on LDI, with a demarcated predominantly yellow area of at least 25cm^2^.

The colour codes representing the perfusion units (PU) and healing potential are as follows [8, 23]:

Red/pink: PU 441–2500, healing potential within 14 days;Yellow/green: PU 201–440, healing potential about 14 to 21 days;Blue: PU 0–200, healing potential more than 21 days.

Exclusion criteria:

Frostbite injury [24];Burns suitable for primary closure;Patients unable to complete the Patient and Observer Scar Assessment Scale (POSAS) due to language restrictions or legal incompetence.

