#### Burn wound area selection

Based on the healing potential, the attending physician will determine whether the patient has burns that meet the inclusion criteria. A maximum of two inclusion criteria-meeting burns per patient are followed for the study.

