### Primary outcome

#### Scar quality

The primary outcome measure of the study is long-term scar quality assessed with the POSAS (generic version, 3.0) 12 months after discharge. The POSAS is a widely used scar quality measurement instrument that comprises two separate scales: the Patient Scale and the Observer Scale [30]. The Patient Scale includes 17 questions about visual, tactile and sensory characteristics, and the overall opinion. The Observer Scale includes eight questions assessing the scar’s pigmentation, vascularity, surface level, surface texture, firmness, adherence, tension, and overall opinion. Each item is rated on a five-point scale. The lowest score is ‘1’, which corresponds to the situation of normal skin (i.e. normal pigmentation, no itching). Score ‘5’ equals the largest difference from normal skin (i.e. the worst imaginable scar or sensation) [30].

The Patient Scale is assessed by the patient, and two independent observers assess the Observer Scale on the study area(s). The assessment is mostly done during the standard 12-month outpatient appointment by the attending burn physician(s) and/or by members of the research team. If there is no standard 12-month outpatient appointment planned, the patient is invited to attend the clinic for the scar quality assessment, for which travel and parking expenses are reimbursed. All members of the research team and the burn physicians are trained to assess scar quality with the POSAS. Each burn centre’s highly experienced head of research provides a POSAS training on the latest version: POSAS 3.0 [30].

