#### Patient and treatment characteristics

Demographics, burn characteristics, and treatment characteristics will be obtained from DBR R3.

Demographics: age, gender, medical history, referral, burn centre. Burn characteristics: TBSA, date of burn injury, burn localisation, burn aetiology, inhalation injury. Treatment characteristics: date of initial surgical intervention and thereby time till first surgical intervention (in days), admission on Intensive Care Unit (ICU), ventilation, topical wound treatments, and wound debridement method, type of grafting, other surgical interventions if applicable.

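### Scar, healing and infection are scored on one or two selected burn areas, but the listed covariates omit the size and LDI class of those areas, so area size and site may confound the adjusted comparison

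*Protocol article*

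**What the plan says.** **Entry (Protocol article, Criteria).** Every burn must meet one size rule: "Burns with a size of >2.5 centimetres diameter". A wholly yellow burn has no further area requirement: "Deep partial-thickness burn: yellow wound area on LDI with healing potential between 14 and 21 days". Burns mixed with red or with blue must also come "with a demarcated predominantly yellow area of at least 25cm^2". No maximum size is given for either kind.

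**What is scored (Burn wound area selection; Scar quality; Clinical outcomes).** "A maximum of two inclusion criteria-meeting burns per patient are followed for the study". The POSAS Observer Scale, time to healing and wound infection are all tied to these study areas, not to the patient's burns as a whole.

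**What is available for adjustment (Patient and treatment characteristics; Statistical analysis).** "Demographics, burn characteristics, and treatment characteristics will be obtained from DBR R3". The burn items are listed as "Burn characteristics: TBSA, date of burn injury, burn localisation, burn aetiology, inhalation injury". The Statistical analysis section then corrects for patient, burn and centre characteristics by regression, without a closed list of covariates.

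**How groups arise (Study design; Selection).** There is no randomisation. Each nine-month period has a preferred strategy, physicians may depart from it, and patients are grouped by the treatment they received.

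**Homogeneity (Discussion).** The article counts the homogeneity of the study areas as a strength and supports it by their comparable healing potential.

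**The concern.** The outcome belongs to a particular patch of skin, while the one listed measure of extent belongs to the whole body. Two patients with the same TBSA may have a small scored spot in one case and a large scored field in the other. No listed covariate separates them by size. Whether localisation separates them by site depends on whether the registry codes it for the scored burn, which the article does not say.

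In a randomised trial this would mainly cost precision. Here regression adjustment is the main protection of the primary comparison. If area size or site influences both the choice of treatment and the scar score, the adjusted difference in POSAS carries part of that influence. The same applies to time to healing and infection. The homogeneity statement may also reassure a reader that the scored areas are alike in a respect that the entry rule does not secure.

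**Working it through.** **Reproducing the plan's figure.** The article expects at most 204 patients. This is an extrapolation from registry and trial counts that are not shown, so it cannot be reproduced. It is used below only to scale an illustration, as 204/2 = 102 per group.

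**1. Entry thresholds (from Criteria).**
- Wholly yellow burn, circular, 2.5 cm diameter: π × (2.5/2)² = 4.91 cm².
- Mixed burn: 25 cm² of yellow, equal to a circle of 2 × √(25/π) = 5.64 cm diameter.
- Ratio: 4.91/25 = 0.196, or about 1 to 5.1.
- The article does not say which diameter is meant. If 2.5 cm is the longest axis of an ellipse with axis ratio 1 to 0.5, the ratio is 0.20 to 0.10. If it is the shortest axis with elongation 1 to 2, the ratio is 0.20 to 0.39.

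**2. Can TBSA stand in for area size?** Assume a body surface of 1.8 m² = 18,000 cm² (not in the documents).
- 4.91/18,000 = 0.03% TBSA.
- 25/18,000 = 0.14% TBSA.

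The thresholds differ by about 0.1% of body surface, so TBSA cannot distinguish areas of these sizes. In a patient with several burns it need not follow the scored area at all.

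**3. Illustration of residual confounding.** All inputs except 204 are assumed. Let *b* be the effect of a large or adverse-site area on POSAS, in SD units, and *d* the difference between groups in how common such areas are. Assume that the listed covariates remove none of it, that each patient contributes one scar, and that the split is equal with no losses.
- Bias = *b* × *d*.
- SE = √(2/102) = 0.140 SD.
- False-positive rate = P(|Z| > 1.96), with Z centred at bias/SE.

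| b (SD) | d | Bias (SD) | False-positive rate |
|---|---|---|---|
| 0 | any | 0 | 5.0% |
| any | 0 | 0 | 5.0% |
| 0.2 | 0.1 | 0.02 | 5.2% |
| 0.2 | 0.3 | 0.06 | 7.1% |
| 0.5 | 0.1 | 0.05 | 6.5% |
| 0.5 | 0.2 | 0.10 | 11.0% |
| 0.5 | 0.3 | 0.15 | 18.8% |

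**4. How large could *d* be?** Suppose the two periods are of equal size, a fraction *r* crosses over in each, and crossovers are perfectly sorted by area. If *p* is the overall frequency of such areas, one group ends with *p* + *r* and the other with *p* − *r*, so *d* is at most 2*r*. A value of 0.3 needs *r* = 0.15 with perfect sorting. An assumed *r* of 0.10 caps *d* at 0.20 and the bias at 0.5 × 0.20 = 0.10 SD. This bound covers sorting by crossover only, and the crossover rate is not known.

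**5. Direction.** Criteria admits patients who stay at least 24 hours or who have an operation planned. A patient with a small burn who needs no admission therefore enters only through planned surgery, which could place small areas among operated patients. Clinicians leaving small or less critical areas to heal would push the other way. Nothing in the article decides between the two.

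**The case against.** The strongest reply has four parts.

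- **The covariate list is not closed.** The article condenses a fuller plan, and exact covariates are usually set in the analysis plan, which is not shown. It would be wrong to infer that adjustment is confined to TBSA and localisation: aetiology, inhalation injury, patient characteristics and centre are also within the stated adjustment. This stands. The point is therefore limited to what the list contains, to the entry rule, and to the homogeneity claim, all of which the article does state.
- **Localisation may already be that of the scored burn.** A reader might infer that it describes the patient as a whole, because the section heading concerns the patient and the items come from a registry. The article says neither. Failure to adjust for site is not shown, only that adjustment for the scored site is not assured.
- **The two thresholds apply equally to both groups.** A reader might infer that the five-fold difference itself confounds. It does not. It widens the range of areas, and confounding also needs an imbalance between groups and an effect on the score. A larger minimum for mixed burns is also defensible, since the yellow part must be separable.
- **Treatment is set mainly by period, and departures are meant to be rare.** This limits the imbalance, as step 4 of the working shows. It does not remove it: the crossover rate is unknown, both periods allow departures, and the planned-surgery entry route is a second way for size and treatment to become linked.

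The exclusion of burns suitable for primary closure may also remove some very small burns. It sets no size floor, so 4.9 cm² is a geometric minimum and says nothing about typical areas.

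**Conclusion.** The point holds as a limited and inexpensive improvement to the adjustment. The scored area's size and LDI class are not among the listed characteristics, TBSA is a poor substitute for that size, and localisation is not stated to be that of the scored area. With groups formed by treatment received, area size and site may confound the adjusted comparison. The claimed homogeneity is supported for healing potential but not for size.

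The documents contain nothing from which the amount of bias can be computed. Under the assumed inputs it runs from nil to about 0.15 SD, with a false-positive rate of 5% to 19%. The upper end needs a 0.5 SD effect, a 30-point imbalance, no help from the listed covariates and 102 patients per group.

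A reader might go further and conclude that the primary result will be biased against early excision. That needs small or less critical areas to be left to heal more often, which the documents do not show, and the entry rule gives a plausible route to the opposite.

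**What to change.** 1. Record three items for each study area: its size, read from the qualifying LDI image; its body site; and its LDI class (pure yellow, mixed with red, mixed with blue).
2. Enter these with TBSA in the adjusted models for POSAS, time to healing and infection. Where a patient contributes two areas, the items must be attached to the area and not averaged over the patient.
3. Add a sensitivity analysis restricted to study areas with at least 25 cm² of yellow, whatever the LDI class.
4. Qualify the Discussion so that homogeneity refers to healing potential, and report the distribution of area size by treatment group.

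**Cost.** Data extraction for at most two areas per patient, a few extra model parameters, and wording. No new patients, visits or procedures are needed. Reading size afterwards assumes that the qualifying LDI images have been kept, which the article does not state. The site should be known for each scored scar. The restricted analysis will lose an unknown number of areas and should be read as a check, not as a replacement for the main result.

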### Standard care

#### Laser Doppler Imaging

The assessment of healing potential is critical for clinical decision-making [25]. LDI is considered the most accurate method for predicting the burn wound healing potential [26]. The LDI technique is based on the Doppler principle with a laser beam that reflects moving objects, such as erythrocytes. The amount of reflection on photodiodes displays dermal perfusion on a scale, from which the healing potential is derived [27]. LDI shows an accuracy of more than 95% and is mostly used in combination with bedside clinical examination [28]. Especially for deep partial-thickness burns clinical assessment of burn depth can be challenging. Yet, an accurate burn depth assessment is important to determine the appropriate treatment.

Patients receive an LDI scan upon indication of the attending physician. The moorLDI2-Burn Imager^™^ scan (Moor Instruments, Axminster, UK) is conducted between 48 hours and five days post-burn for optimal accuracy [29]. The LDI scan procedure is standard care in the Netherlands and performed in daily clinical practice by experienced and trained personnel.

#### Burn wound area selection

Based on the healing potential, the attending physician will determine whether the patient has burns that meet the inclusion criteria. A maximum of two inclusion criteria-meeting burns per patient are followed for the study.

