## Materials and methods

### Study design

A multicentre prospective study with a 12-month follow-up period will be conducted in the three Dutch burn centres: Maasstad Hospital Rotterdam, Red Cross Hospital Beverwijk, and Martini Hospital Groningen. Patients with deep partial-thickness burns, scanned as yellow by Laser Doppler Imaging (LDI), will be monitored during 18 months; two nine-month periods with either therapy as the treatment of choice in one of the periods. This time period was chosen based on expected numbers and project logistics, such as staffing. Standard care in the Netherlands for deep partial-thickness burns is predominantly conservative treatment with delayed excision and grafting if needed. However, early excision and grafting is applied if deemed more appropriate for a specific patient. The first nine-month period (July 15^th^ 2022 to April 14^th^ 2023) this strategy is followed. In the following nine-month period (April 15^th^ 2023 to January 14^th^ 2024) clinical practice will be changed: early excision and grafting will be the primary treatment. However, in specific cases e.g. based on clinical expertise, conservative treatment can be applied. Depending on the received treatment, patients will be categorized as either the conservative treatment group with delayed excision and grafting if needed, or the early excision and grafting group.

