### Study status and timeline

Data collection from DBR R3 and BORN started on July 15^th^ 2022. Inclusion of participants started after approval of the local review boards of all participating hospitals on June 25^th^ 2023. The first patient inclusion and 12-month POSAS was conducted on June 30^th^ 2023. Data collection and participant selection is expected to be completed in January 2025.

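### No rule or time point fixes which burns are scored for the primary outcome, and the stated inclusion dates leave room to choose them once their course is known

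*Protocol article*

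**What the plan says.** Under Burn wound area selection, the protocol article says that, on the basis of healing potential, "the attending physician will determine whether the patient has burns that meet the inclusion criteria". It then sets the cap: "A maximum of two inclusion criteria-meeting burns per patient are followed for the study". That section gives no order of preference among qualifying burns, no criterion for following one rather than two, and no time by which the choice is recorded.

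The primary outcome is tied to these burns. Under Scar quality, "two independent observers assess the Observer Scale on the study area(s)", and the observers may include the attending burn physicians. Under Clinical outcomes, time to healing and wound infection also refer to the study areas. The Selection section states that there is no randomisation or blinding, and that a patient is included once written consent has been given.

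Under Study status and timeline, "Inclusion of participants started after approval of the local review boards of all participating hospitals on June 25", 2023, and "The first patient inclusion and 12-month POSAS was conducted on June 30", 2023. Participant selection is expected to run until January 2025. Study design dates period 1 from 15 July 2022 to 14 April 2023 and period 2 from 15 April 2023 to 14 January 2024.

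**The concern.** The choice of study area decides which scar the primary outcome describes. If that choice is open, and is made by someone who knows the treatment and how each burn healed, the scored scar can be a better or worse example of the patient's burns for reasons unrelated to treatment strategy.

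The planned regression adjusts for patient, burn and centre characteristics. It cannot undo selection on the outcome itself. If the opportunity to select differed between the compared groups, a difference could appear, or be hidden, without any treatment effect.

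**Working it through.** The plan gives no figure to reproduce here. The check compares its dates with its own clinical windows and then illustrates what free selection could do.

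**Inputs**
- Period 1: 15 July 2022 to 14 April 2023. Period 2: 15 April 2023 to 14 January 2024, 275 days (Study design).
- Inclusion opened on 25 June 2023 (Study status and timeline).
- LDI scan between 48 hours and 5 days post-burn (Laser Doppler Imaging).
- Delayed grafting considered if the burn has not healed after 14 to 21 days (Procedures).

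**Period 1**
- Last day of period 1 to opening of inclusion: 14 April to 25 June 2023 = 72 days.
- First day of period 1 to opening: 15 July 2022 to 25 June 2023 = 345 days.
- The most recent period-1 patient was therefore at least 72 − 5 = 67 days past the LDI window and 72 − 21 = 51 days past the 21-day point at inclusion.

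That these burns had healed or been grafted by then is inferred from the elapsed time. It is very likely, but not stated.

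**Period 2**
- 15 April to 25 June 2023 = 71 days, so 71/275 = 26% of period 2 precedes the opening of inclusion.
- Burns more than 5 days old at opening: 71 − 5 = 66 days of period 2, or 66/275 = 24%.
- Burns more than 21 days old at opening: 71 − 21 = 50 days, or 50/275 = 18%.

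These are minimum figures. The first inclusion coincided with a 12-month scar assessment, and participant selection continues a year beyond the end of period 2. Later period-2 patients could therefore also have been included long after their scan.

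**Where the choice is real**
- One qualifying burn followed: no choice.
- Two qualifying burns, both followed: no choice, shift zero.
- Two qualifying, one followed; or three or more qualifying: a choice exists.

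The documents do not say how many patients fall into the last category.

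**Illustration (assumed model)**
Let the scar scores of a patient's burns be independent and normal with a common SD, and let selection be purely on outcome. A neutral choice has expected shift 0.
- Worst two of three: the expected maximum of three is 3/(2√π) = 0.846 SD and the expected middle value is 0, so the mean is 0.846/2 = 0.42 SD.
- Worst two of four and of five: 0.66 and 0.83 SD (simulation, 400,000 draws).
- Worst one of two: 1/√π = 0.56 SD.

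With within-patient correlation ρ these figures are multiplied by √(1 − ρ). At ρ = 0.5, worst two of three gives 0.42 × 0.71 = 0.30 SD. Picking the best burns gives the same sizes with the opposite sign. The effect on a group mean is the shift times the share of the group selected in this way. At assumed shares of 20% and 50%, 0.42 SD becomes 0.08 and 0.21 SD.

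**The case against.** The case on the other side has four parts.

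First, the selection section gives the physician a judgement of eligibility based on the scan. It does not say in words that the physician picks among qualifying burns. This is fair, although under that heading, and with no other rule or person named, it is the natural reading.

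Second, a journal article condenses a fuller protocol, which may hold the tie-break rule. Silence alone would indeed not be a finding. The point stands because the dates the article does state, together with the absence of blinding, leave outcome-dependent choice open for the area that carries the primary outcome.

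Third, late consent is not late choice of area. Consent concerns the additional 12-month measurements. Registry data collection began on the first day of period 1, eligibility rests on an early scan, and re-epithelialisation of the study areas is recorded at each wound inspection. All of this is compatible with marking the areas during acute care. It stands as a limit on the claim: the text allows early designation but does not state it.

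Fourth, a reader might infer that areas were picked with the outcome known in period 1 and not in period 2, so that the treatment comparison is biased. The documents do not support that. They do not say when areas were designated, part of period 2 is affected too, and patients are grouped by treatment received, with both treatments possible in both periods. A reader might also take the shift for one of two burns as typical. The cap allows both to be followed, in which case the shift is zero.

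**Conclusion.** The point holds as an unclosed route to bias, not as a demonstrated bias. The choice of burns for the primary outcome rests on an unblinded physician's judgement, with a cap of two and no rule or time point. All period-1 patients, and those burned in about the first quarter of period 2, were included after the LDI window, and most or all of them after the course of their burns was known.

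The risk is confined to patients with three or more qualifying burns, or with one of two taken. Its size and direction cannot be derived from the documents. The 0.42 SD for the worst two of three assumes independent normal scores and selection purely on outcome. It shows that unrestricted selection could matter and is not an estimate for this study. If areas were in fact marked at the scan, the timing concern largely falls away and only the missing rule remains.

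**What to change.** Define study areas from the LDI scan by a fixed rule, for example the largest qualifying predominantly yellow area, then the next largest, and record them before the 12-month scar assessment. For patients included after the acute phase, have an existing research-team member apply the rule to the scans, where these were retained, without sight of treatment, healing or scar records.

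Where areas were already marked at the scan, or already scored, state when and by whom, and run a sensitivity analysis restricted to areas that match the rule.

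The cost is a short addition to the selection section, a re-read of existing scans and one extra analysis. The downside is that a rule-based area may matter less to the patient than one picked at the bedside. Scans may also not be retrievable for everyone, and some areas already scored may not match. Whether one or both areas enter the primary analysis is a separate decision that this change does not settle.

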### Secondary outcomes

#### Clinical outcomes

Time to wound healing of study area(s): this is defined as the number of days between burn injury and re-epithelialisation of >95% of the wound surface. Progression of re-epithelialisation is assessed by an experienced burn specialist and reported after every wound inspection.

Wound infection of study area(s): the attending physician will document whether a wound infection has occurred, based on inflammation characteristics (rubor, dolor, calor, tumor, functio laesa) in combination with a positive wound culture.

As of 2009, patient and clinical characteristics are prospectively registered in the Dutch Burn Repository (DBR) R3 in the three Dutch burn centres. Clinical outcomes that will be obtained from DBR R3 are mortality (during admission), time to first excision and grafting, length of hospital stay, length of ICU stay, readmission, reoperation, blood transfusion requirements, wound complications (e.g. graft failure), sepsis, shock, reconstructive surgery, number and timing of outpatient visits. To assess the amount of clinical topical wound treatments, the length of hospital stay will be used as a proxy.

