### Statistical analysis

For the statistical analysis descriptive statistics will be used. All parameters will be tested for normality. Depending on the distribution of the data, a mean and standard deviation (normal) or a median and interquartile range (skewed) will be displayed. Differences between the two treatment strategies for the primary outcome measure scar quality and other outcomes will be analysed using two-sided T-test (normally distributed continuous data) or Mann-Whitney U-test (skewed continuous data), and two-sided Chi-square test or Fisher’s exact test (categorical data). Differences between groups in time to event outcomes (i.e. time to surgical intervention and time to wound healing) will be analysed using Kaplan-Meier regression. To correct for the possible influence of patient, burn, and burn centre characteristics on the results, multivariate linear regression (continuous data), multilevel logistic regression (categorical data), and Cox regression (time to event data) will be used. If possible, exploratory analyses will be done on the 10–14 day surgery group. Data analysis will be performed using IBM Statistical Package for the Social Sciences (SPSS) version 26 (SPSS, Chicago, IL, USA) and Python (Python Software Foundation, Delaware, USA).

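### Up to two burns per patient are followed, but the unit of analysis is not stated and the methods named for the primary outcome and for healing time assume independent records

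*Protocol article*

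**What the plan says.** All places are in the Protocol article.

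- **Burn wound area selection:** "A maximum of two inclusion criteria-meeting burns per patient are followed for the study".
- **Scar quality (primary outcome):** two observers score the Observer Scale for the study area or areas, so a patient with two areas yields two sets of scores.
- **Clinical outcomes:** time to wound healing and wound infection are also defined for the study area or areas. Other outcomes, such as length of stay and time to first excision and grafting, come from the registry and are naturally one per patient.
- **Study design:** the group belongs to the patient: "Depending on the received treatment, patients will be categorized as either the conservative treatment group with delayed excision and grafting if needed", or else the early surgery group.
- **Sample size:** the forecast is counted in patients, at most 204 over 18 months.
- **Statistical analysis, unadjusted:** "Differences between the two treatment strategies for the primary outcome measure scar quality and other outcomes will be analysed using two-sided T-test" or, for skewed data, the Mann-Whitney test. Chi-square or Fisher's exact test is named for categorical data and Kaplan-Meier for healing time.
- **Statistical analysis, adjusted:** "multivariate linear regression (continuous data), multilevel logistic regression (categorical data), and Cox regression (time to event data) will be used". The stated purpose is correction for patient, burn and centre characteristics. Correlation between two burns of one patient is not mentioned.

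No section says how two areas become one value, names an index area, or adds a patient term or clustered variance for the continuous and time-to-event outcomes.

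**The concern.** Two burns on one person share that person's healing biology, and on the Patient Scale they share the rater. Their outcomes are therefore likely to be positively correlated. Because the group is set per patient, both burns fall on the same side of the comparison, so the second burn adds less information than a burn from a new patient would. A t-test, Mann-Whitney test, ordinary linear regression or standard Cox model fitted to one row per area counts it in full.

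Confidence intervals would then be too narrow, and the primary comparison would reject too often. The same applies to healing time and, in the unadjusted chi-square or Fisher test, to wound infection.

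The section does more than stay silent. It assigns a method to each type of outcome and reserves the multilevel form for categorical data, so an analyst who follows it with area-level rows has no instruction that would correct the error.

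**Working it through.** **Figures in the plan.** The article gives no alpha, share of two-burn patients, within-patient correlation or power calculation. Its only figure is the forecast of at most 204 patients, which cannot be rebuilt because the source counts are not given. There is thus no plan figure to reproduce on this point.

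**Inputs**
- Areas per patient: 1 or 2 (Burn wound area selection).
- Both areas in the same group (Study design).
- Patients: 204 (Sample size), split 102/102 by assumption.
- Two-sided alpha 0.05: assumed.
- Share of patients with two areas, p: assumed 0.2 to 1.0.
- Within-patient correlation, ICC: assumed 0.3 to 0.7.

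**Formulas**
- Design effect: DE = 1 + ICC × (E[m²]/E[m] − 1), with m the number of areas. Since E[m] = 1 + p and E[m²] = 1 + 3p, this is DE = 1 + ICC × 2p/(1 + p).
- True SE / naive SE = √DE.
- Actual type I error = 2 × (1 − Φ(1.96/√DE)).

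**Example, p = 0.5 and ICC = 0.5**
- DE = 1 + 0.5 × 1/1.5 = 1.333, and √DE = 1.155.
- Type I error = 2 × (1 − Φ(1.697)) = 0.090.
- 204 × 1.5 = 306 areas carry the information of about 306/1.333 ≈ 229 independent ones.
- Difference detectable at 80% power: naive (1.96 + 0.84) × √(4/306) = 0.32 SD; true 0.32 × 1.155 = 0.37 SD.

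**Range**

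| p | ICC | DE | True SE / naive SE | Type I error |
|---|---|---|---|---|
| 0.2 | 0.3 | 1.100 | 1.05 | 0.062 |
| 0.2 | 0.5 | 1.167 | 1.08 | 0.070 |
| 0.2 | 0.7 | 1.233 | 1.11 | 0.078 |
| 0.5 | 0.3 | 1.200 | 1.10 | 0.074 |
| 0.5 | 0.5 | 1.333 | 1.15 | 0.090 |
| 0.5 | 0.7 | 1.467 | 1.21 | 0.106 |
| 1.0 | 0.3 | 1.300 | 1.14 | 0.086 |
| 1.0 | 0.5 | 1.500 | 1.22 | 0.110 |
| 1.0 | 0.7 | 1.700 | 1.30 | 0.133 |

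**Simulation check** (normal outcomes, no treatment effect, 102 patients per group, 8000 runs for each of six scenarios)
- At p = 0.5, ICC = 0.5, the area-level t-test rejects in 0.090 of runs and the Mann-Whitney test in 0.088.
- At p = 1, ICC = 0.7, they reject in 0.135 and 0.132. Both agree with the formula.
- A t-test on one mean per patient rejects in 0.0465 to 0.0515 of runs over the six scenarios. The simulation error is about √(0.05 × 0.95/8000) = 0.0024, so this is the nominal level.

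These figures are for a comparison of means. For Cox regression and the test on infection the direction is the same, but the size was not computed.

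**The case against.** A reader might infer that the plan does analyse each burn as an independent observation, so that the primary test is certainly anti-conservative. The article does not say that. It says that up to two burns are followed, and it never names the unit of analysis. Patients are put into groups, and patients are counted in the sample size. All this is compatible with one value per patient, in which case the check above shows no inflation. The error is therefore conditional.

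A reader might also infer that two areas of one patient could be treated differently and end up in different groups. No section says so; the group is set per patient. If it did happen, positive correlation within such pairs would make the naive standard error of the difference too large, not too small. It is no part of this point.

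It can further be said that an article condenses the full plan, that the unit of analysis is a common analysis-plan detail, and that the multilevel logistic model shows some thought about clustering. This would answer the point if the article merely left the method open. But it names a method for each outcome type and attaches the multilevel form to only one of them, at an unstated level. Nothing elsewhere in the article resolves that asymmetry. Nor does the patient-level reading settle everything: without a rule, the way two scars become one score can be chosen after the scores are known, in a study that is neither randomised nor blinded.

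**Conclusion.** The point holds in conditional form. The plan follows up to two areas per patient, does not state the unit of analysis, and names independence-based methods for the continuous primary outcome and for healing time. The unadjusted tests for area-level infection have the same gap.

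If areas are analysed as separate records, the naive standard error is about 5% (1 − 1/1.049) to 23% (1 − 1/1.304) below its true value, and the type I error is about 6% to 13% instead of 5%. This rests on the assumed alpha, share of two-area patients and correlation, none of which the article gives. With few two-area patients and weak correlation the effect is small. Outcomes recorded once per patient are not affected.

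**What to change.** State the unit of analysis for every outcome recorded by study area, and then take one of two routes.

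1. **One value per patient.** Use the mean of the areas, or an index area chosen by a rule fixed before outcome assessment. For scar quality the tests and linear model already named can then stay. For healing time and infection, an index area allows the same.
2. **Areas as the unit, with clustering modelled.** Use a linear mixed model with a patient random intercept for POSAS, a patient-clustered (robust) or shared-frailty Cox model for healing time, and a patient-level random effect or GEE for wound infection. The same models without covariates replace the unclustered t-test, Mann-Whitney and chi-square or Fisher tests. Kaplan-Meier curves can remain as description.

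In either case, say which level the multilevel logistic model refers to.

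The cost is a few sentences in the plan and a little more analysis work. No new data are needed. Intervals become slightly wider than under the naive analysis; an index area also leaves the second area out of the main comparison.
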